**Protocol summary**

| **Protocol number** | TG0912ALS-3 |
| --- | --- |
| **Protocol name** | A Randomized, Double-Blind, Placebo-Controlled, Multicenter Phase II Clinical Trial of Allisartan Isoproxil in the Clinical Efficacy and Safety Treatment of Primary Hypertention Patients at Low-Medium Risk |
| **The version number/date** | The 1.2 eidtion, Aug, 06th, 2009 |
| **Sponsor** | Shenzhen Salubris Pharmaceuticals Co.,Ltd  Shanghai ALLIST Medicine Technology Co., Ltd. |
| **Clinical trial staging** | Phase II |
| **Indications** | Medium and lower risks of primary hypertension |
| **Experimental objective** | **The primary objective:**  The primary objective was to compare the change of seated diastolic blood pressure from baseline to 8weeks in primary hypertensive patients with medium and low risks treated with 240 mg Allisartan Isoproxi tablet (ALS-3) and placebo to confirm the absolute antihypertensive effect of the Allisartan Isoproxi tablet (240 mg).  **The secondary objective:**  The secondary objective was to compare the following aspects of primary hypertensive patients at low-medium risk treated with 240 mg Allisartan Isoproxi tablet (ALS-3) and placebo:   - The change of trough mean seated DBP after 4 weeks treatment; - The change of trough mean seated SBP after 4 ,8weeks treatment; - Effective rate after 4,8 weeks treatment (Seated position SBP/DBP＜140mmHg/85mmHg, or SBP decreasing of 20 mm Hg and/or DBP decreasing 10 mm Hg); - The change of trough mean seated SBP/DBP after 4 ,8weeks treatment in effective patient; - Safety evaluation after 8 weeks. |
| Experimental design | A randomized, double-blinded, placebo-controlled, multi center clinical trial |
| **Total number of cases** | There was 1 treatment group and 1 placebo group. One hundred and eight cases of patients in each group can be evaluated, and a total of 216 cases of patients can be evaluated. Considering a loss rate of 20%, a total of 260 subjects were needed to be enrolled. |
| **Research center number** | Eight |
| **Criteria of case selection** | **Inclusion criteria:**   1. Male and female aged 18 to 70 years old; 2. BMI within 18.5-26kg/m2; 3. Mild to moderate essential hypertension according to the diagnostic criteria of China (2005); 4. The mean seated blood pressure after 2-week washout period with placebo (the blood pressure should be detected 3 times every 2 minutes after 5-minute resting in sitting position and then take the mean value) should be 140mmHg ≤SBP<180mmHg and 90mmHg ≤DBP< 110mmHg; 5. Able and willing to provide signed informed consent.   **Exclusion criteria:**   1. Having been diagnosed or suspected as secondary hypertension; 2. The difference of systolic blood pressure in seated place measured for three consecutive times is greater than 20 mmHg, and the difference of diastolic pressure is greater than 10 mmHg; 3. Sick sinus syndrome, II~III atrial ventricular block, atrial flutter, atrial fibrillation, or other malignant arrhythmia; 4. Aneurysm in conducting artery or dissecting aneurysm, percutaneous tranluminal coronary angioplasty (PTCA) or other cardiac surgery; 5. Unstable angina pectoris, acute myocardial infarction, cardiac failure, and cerebral accidents within recent 6 months; 6. Asthma or moderate to severe chronic obstructive lung disease; 7. Uncontrolled diabetes, FBG≥11mmol/L or with complications (degenerative nephritis and peripheral neuropathy); 8. Renal arterial stenosis; 9. Renal inadequacy ( Cr>1.5×ULN (the upper limit of the normal range); 10. Serious hepatopathy or hepatic inadequacy (ALT, AST or TBIL> 2×ULN); 11. Electrolyte disturbances (blood potassium or sodium abnormality); 12. Subjects with lower blood volume; 13. Female subjects with pregnancy or in lactation; 14. Subjects with drug or alcohol dependence; 15. Concomitant treatment with other drugs which will affect the blood pressure; 16. Subjects with resistant hypertension; 17. Allergy to any ingredient in the study; 18. attend other clinical trail within 3 month; 19. Suspected as white overcoat hypertension according to the judgment of investigators; 20. Subjects are thought unsuitable for the study by investigators.   **Criteria of subject exiting:**   - - - 1. Withdrawal the study under patients willing will;       2. Occurrence of serious adverse events or intolerable adverse events;       3. Seated SBP ≥ 180 mmHg or seated diastolic blood pressure ≥ 110mmHg during the study;       4. Serious violations of inclusion and exclusion criteria;       5. Poor compliance to the protocal;       6. Lost of follow-up;       7. Other reasons |
| **Research drugs** | The research drug: Allisartan Isoproxi, tablets, 80 mg/tablet;  Placebo: Allisartan Isoproxi placebo, tablets, 80 mg/ tablet. |
| **Grouping of tests** | After 2 weeks washout period (taking placebo), the 260 subjects meeting the inclusion criteria and not meeting the exclusion criteria were randomly assigned to one of the following two groups at a ratio of 1:1:   - The test group A: Allisartan Isoproxi tablet 240 mg (Allisartan Isoproxi tablet 80 mg, 3 tablets), once a day, taking the medicine fasting orally half an hour before breakfast; - The placebo group B: Allisartan Isoproxi tablet placebo 240 mg (Allisartan Isoproxi tablet placebo 80 mg, 3 tablets), once a day, taking the medicine fasting orally half an hour before breakfast;   Patients finished the double blind randomized studies at 8 weeks could participate in additional 56 weeks safety observation under patients own free will.The participants will take Allisartan Isoproxi tablets 240 mg (Allisartan Isoproxi tablets 80 mg, 3 tablets) once a day. |
| Research steps | The present study inlcuded 2 weeks washout period and 8 weeks double-blind randomized treatment period. Interview is needed after treatment for 2 weeks, 4 weeks and 8 weeks. After finishing the double blind randomized treatment period, there is a safety observation period of 56 weeks. There is an interview every 8 weeks.  All the subjects signed the informed consent prior to screening.  Screening/cleaning periods (Interview 1, -3 ~ 0 week)  The starting of giving the treatment with the research drug in the first 3 weeks, and before taking placebo (that is -3 weeks to -2 weeks), the following screening assessment projects should be finished:   - Demographic data including gender and age (date of birth) of the subjects; - Height, weight, waist circumference, smoking and drinking status; - Collecting of the disease history: inquire and record the history of hypertensive disease of the subjects (including the time of illness of hypertension and levels of blood pressure), family history, complications/disease and treatment history, other previous disease and treatment history, allergic history; - Physical examination: conducting of the physical examination of all body systems; - Resting seated blood pressure and measurements of heart rate; - Laboratory and auxiliary examinations: including urine pregnancy test (limited to women of childbearing age), whole blood test, urine routine test test, liver function, kidney function, fasting blood glucose, blood lipid, blood electrolyte and a 12-lead electrocardiogram.   For the patients preliminarily screened as the medium and low risk primary hypertension basically meeting the inclusion criteria but not meeting the exclusion criteria, they entered the placebo washout period of 2 weeks (-2 ~ 0 weeks). The patients will provide and take placebo for 2 weeks. At the same time, diary cards will be given.  In addition, the adverse events and concomitant treatments will be recorded between the signing of the informed consent and taking placebo for 2 weeks.  Baseline (Interview 2, 0 week)  After the subjects took the placebo for 2 weeks, the following aspects should be conducted:   - Measurement of the resting sitting blood pressure and heart rate: the measurement method was as the same as that of the screening period; - Auditing the inclusion/exclusion criteria, the qualified candidates were given random numbers (i.e. drug numbers) according to the order of entering groups from small to large; - According to the random number, the research drugs for the first ~ second week treatment period were provided (including alternative medicine of 3 days); - Recovery of the research drugs of 2 weeks in the placebo washout period; - Transfering and recording of the diary card of subjects; - Recording adverse events and concomitant treatments.   The treatment period (Interview 3, 2 weeks ± 3 days)   - After the subjects taking the research drugs in the double-blind randomized treatment period for 2 weeks, the following aspects were needed to be carried out: - Measurment of the resting sitting blood pressure and heart rate: the measurement method was as the same as that of the screening period; - According to the random number, the research drugs for the third ~ fourth week treatment period were provided (including alternative medicine of 3 days); - Recovery and counting of the remainder research drugs in the first and second week; - Transfering and recording of the diary card of the subjects;   Recording adverse events and concomitant treatments.  The treatment period (Interview 4, 4 weeks ± 3 days)   - After the subjects taking the research drugs in the 4 weeks double-blind randomized treatment period, the following aspects were needed: - Measurement of the resting sitting blood pressure and heart rate: the measurement method was as the same as that of the screening period; - Laboratory examinations: urine routine test, liver function, renal function and serum electrolyte; - The research drugs of the treatment period between the fifth week and the eighth week were distributed according to the random number (including the reserve drug for 6 days); - Recovery and counting of the remainder research drugs in the third and fourth week; - Transfering and recording of the diary card of the subjects; - Recording adverse events and concomitant treatments.   Finishing of the random treatment (Interview 5, 8 weeks ± 3 days)  After the subjects taking the research drugs in the double-blind randomized treatment period for 8 weeks, the following aspects were needed to be carried out:   - Physical examination: physical examination of all body systems was conducted including body weight; - Measurements of the resting sitting blood pressure and heart rate: the measurement method was as the same as that of the screening period; - Laboratory and auxiliary examinations: including urine pregnancy test (only limited to women of childbearing age), whole blood test, urine routine test, liver function, renal function, fasting blood glucose, blood lipid, blood electrolyte and a 12-lead electrocardiogram. - Recovery and counting of the remaining research drugs of the fifth ~ eighth week; - Distribution of Allisartan Isoproxil tablets for 9 weeks’ dose; - Recovery, transfer and recording the diary cards of the subjects; - Recording of the adverse events and concomitant treatments.   Safety observation period (Interview 6-11, 9-56 weeks, one interview for every 8 weeks, the window period ±7 days)  In order to observe the long-term efficacy and safety of the research drugs, all the subjects participated in the research of the safety observation period of 56 weeks on a voluntary basis after they finished the double-blind randomized study of 8 weeks, during which every subject would accept one treatment of 240 mg Allisartan Isoproxi tablet daily. The subjects should visit the research doctor every 8 weeks:   - Measurement of resting sitting blood pressure and heart rate: the measurement method was as the same as that of the screening period; - Laboratory examination was conducted when it was necessary: urine routine test test, liver function, renal function and serum electrolyte; - Allisartan Isoproxil tablets for 9 weeks dose was distributed; - Recoveryand counting of the remainer research drugs of the past 8 weeks; - Transfer and recording of the diary card of subjects; - Recording of the adverse events and concomitant treatments.   In the review 9, namely the review in which the subjects took the research drugs for 32 weeks of the observation period, in addition to the above items, the following aspects were also needed:   - Physical examination: conducting physical examination of all body systems including weight; - Laboratory and auxiliary examinations: including whole blood test, fasting blood glucose, blood lipid, blood electrolyte and a 12-lead electrocardiogram.   After finishing the safety observation period (review 12, the sixty-fourth week ±7 days.)  After finishing the observation period of 56 weeks of treatment for the participants, the following aspects were needed:   - Physical examinations: physical examination of all body systems including body weight; - Measurement of the resting sitting blood pressure and heart rate: the measurement method was as the same as that of the screening period; - Laboratory and auxiliary examinations: including urine pregnancy test (only limited to women of childbearing age), whole blood test, urine routine test, liver function, renal function, fasting blood glucose, blood lipid, blood electrolyte and a 12-lead electrocardiogram. - Recovery and counting of the remaining research drug of the fifty-seventh ~ sixty-fourth week; - Transfer and recording of the diary cards of subjects; - Recording adverse events and concomitant treatment.   Unplanned interview (when the research required or exiting test in advance)  If subjects needed extra interviews or exiting test in advance, the measures that researchers have taken (including the results of laboratory tests) should be recorded on the original records and the unplanned review table in the case report table.  In addition, when the subjects exited tests in advance before the interview 5 or after they entered the safety observation period and ended early safety observation period, the following aspects should be conducted as far as possible:   - Physical examination: physical examination of all body systems; - Measurement of the resting sitting blood pressure and heart rate: the measurement method was as the same as that of the screening period; - Laboratory and auxiliary examination: including urine pregnancy test (only limited to women of childbearing age), whole blood test, urine routine test test, liver function, renal function, fasting blood glucose, blood lipid, blood electrolyte and a 12-lead electrocardiogram; - Recovery and counting of all the remaining research drugs; - Recovery, transfer and recording of the diary cards of subjects (only applicable to the subjects during the double-blind research period); - Recording adverse events and concomitant treatment. |
| **Therapeutic effect index** | **Primary outcome parameters:**   - The changes from baseline in trough mean seated DBP (23 to 26 hours after the morning dose) to the end of the 8-week double-blind treatment period   **Secondary outcome parameters:**   - The change of trough mean seated DBP after 4 weeks treatment - The change of trough mean seated SBP after 4 ,8weeks treatment - Effective rate after 4,8 weeks treatment - The change of trough mean seated SBP/DBP after 4, 8weeks treatment in effective patient - Note: Effective respond was defined as the seated SBP/DBP<140/85mmHg, or seated SBP decrease≥20mmHg and/or seated DBP≥10mmHg. |
| **Safety index** | Adverse events included the abnormal demonstrations of the clinical symptoms after medication and the changes of clinical significances of physical examination, laboratory examination and ECG. |
| **Statistical analysis** | **Estimation of sample sizes:**  This is a superior efficacy test study. The efficiency test was conducted on the main therapeutic effect index. Setting bilateral α = 0.05, *β* = 0.20, and the standard deviation SD = 7.8 mmHg, the difference of the antihypertensive effect in the two groups were detected as *D* = 3 mmHg. The distribution ratio of the patient cases in the two groups was 1:1. The estimated minimum sample size was 108 pairs. Taking into account of the factors such as dropping, the present research plan included 260 cases into the two groups with 130 cases of patients in the experiment group and the control group, respectively.  **Statistical analysis of the data set:**  Statistical analysis was conducted by using the full analysis set, per-protocol population set and safety data set. The quality control was strictly carried out in the whole process of the data statistics to ensure the authenticity of the assessment of data.  Full analysis set (Full analysis set, FAS): according to the fundamental principle of intention to treat (ITT), all the randomly enrolled subjects with more than one medication administration record and effective evaluation were included in the full analysis set. When selecting full analysis set for analysis, the latest observation LOCF (LOCF) estimation method was adopted for the estimation of the missing values. Full analysis set is the main effectiveness method for the evaluation of population in the present study.  The Per-Protocol set (PPS): PPS included all the subjects with completed prescribed treatment protocal or no serious violations of tests. The exact definition of the serious violations of the scheme will ultimately determined in the data auditing, which generally included the following situations (but they are not limited to these cases): Not meeting the inclusion criteria, having interference treatment after being selected, poor compliance, interview beyond the time window. PP set is a secondary analysis of the crowds of the effectiveness, but if the results were inconsistent with the full analysis set, detailed analysis should be done on the inconsistent results.  Safety data set (Safety Set, SS): the definition of safety data set was the subjects that at least received one time drug treatment.  **Statistical analysis method:**  Statistical analysis was conducted by using the SAS9.13 statistical analysis software for calculation. Quantitative description of the parameters included the calculation of mean, standard deviation, median, minimum value and maximum value. The description of the classified index employed the case number and percentage of the cases.  Descriptive statistics were conducted on the completion of the study. The comparison among groups was conducted on the demographic and baseline characteristics to analyze the equilibrium between groups.  Analysis of the main outcome measures: the main efficacy index will use the test of superiority. In addition, the dereasee value os DBP of each subject after treatment of 8 weeks will also be calculated, and descriptions in each group were done (mean, standard deviation, median, minimum, maximum). Comparisons between groups used analysis of variance considering center effect.  Analysis of the secondary outcome indicators: the center effect was not considered in principle. Comparisons between groups employed the variance analysis, chi-square test or nonparametric statistical method.  Analysis of the safety evaluation: parameters of safety evaluation included adverse events/ adverse drug reaction (ADR)/important adverse events or serious adverse events, physical examination and laboratory examination and a 12-lead electrocardiogram. Detailed description was conducted on the cases of adverse events during the test. The incidence rates of the adverse events between the two groups were summarized and compared. The indexes of laboratory examination were statistically described. The difference between two groups was compared when it was necessary. A detailed description of the laboratory indexes and normal cases before treatments was conducted.  This study did not conduct interim analysis. |

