### The unplanned outside interview

If subjects need extra interviews or early exiting test, the measures having been taken by researchers (including laboratory test results) should be recorded on the original case history and the unplanned interview table in the case report table.

In addition, when the subjects exit the tests early before the interview 5 or enter the safety observation period early to end the safety observation period, the following aspects should be done as far as possible:

- - Physical examination: physical examination of all body systems;
  - Resting sitting blood pressure and heart rate were measured: the measurement method is as the same as that of the screening period;
  - Laboratory and auxiliary examination: including urine pregnancy test (limited to women of childbearing age), whole blood test, urine routine test test, liver function, renal function, fasting blood glucose, blood lipid, blood electrolyte and a 12-lead electrocardiogram;
  - Recovery of all the remaining study drug and counting;
  - Recovery, transcfer and recording of the diary cards of the subjects (only applicable to the subjects during the double-blind study);
  - Recording adverse events and concomitant treatments.

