## Definition and selection of analytic set

The full analysis set and statistical analysis conducted in accordance with the scheme set set and data security. The whole process of statistical data will be strict quality control to ensure the authenticity of the data, assessment.

Full analysis set (Full analysis set, FAS): according to the intention to treat (ITT) principle, the random into groups, and the subjects more than once medication administration record and to evaluate the effectiveness of the enrolled in the full analysis set. In the choice of full analysis set analysis, the missing value estimation, can adopt the LOCF (LOCF) estimation method. Full analysis set is the main evaluation of the effectiveness of the study population.

The project sets (Per-Protocol set PPS): with the scheme set includes all completed treatment provisions scheme or no serious violations of test subjects. The exact definition of serious violations of the scheme will ultimately determine the data audit, generally include the following situations (but are not limited to these cases): Do not meet the criteria, interference treatment in selected, poor compliance, and visit beyond the time window. PP set is a secondary analysis of the crowd's effectiveness, but the results such as the full analysis set is inconsistent, to the detailed analysis of the inconsistent results.

Safety data set (Safety Set, SS): the definition of safety data set for at least the subjects received a drug treatment.

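### The full analysis set asks for more than one medication record, so a randomised subject who takes a single dose is literally left out of the primary analysis (minor; may be a translation slip)

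*Protocol*

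**What the plan says.** The Protocol summary, under the data sets for statistical analysis, presents the FAS as following intention to treat and then sets the entry rule: "all the randomly enrolled subjects with more than one medication administration record and effective evaluation were included in the full analysis set". Section 11.2 (Definition and selection of analytic set) gives the same rule in rougher English: "the subjects more than once medication administration record and to evaluate the effectiveness of the enrolled in the full analysis set". The summary gives the FAS its role as follows: "Full analysis set is the main effectiveness method for the evaluation of population in the present study". For subjects with missing values in that set, "the latest observation LOCF (LOCF) estimation method was adopted for the estimation of the missing values".

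The safety set, defined in the same part of the summary, has a different threshold: "the definition of safety data set was the subjects that at least received one time drug treatment".

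Two other provisions bear on the point. The visit schedule reads: "Interview is needed after treatment for 2 weeks, 4 weeks and 8 weeks". Section 5.3.8 (unplanned interviews) also asks that a resting seated blood pressure be taken, as far as possible, "when the subjects exit the tests early before the interview 5 or enter the safety observation period early to end the safety observation period". A subject who stops before week 2 can therefore still have a post-baseline reading.

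**The concern.** A subject with exactly one dose meets the safety-set rule and fails the FAS rule as written. If the early-exit blood pressure was obtained, that subject has an outcome that last observation carried forward could use, but the entry rule removes the subject before the method applies.

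Stopping after one dose happens after randomisation, and its causes can differ between drug and placebo. Excluding subjects on that basis departs from the principle the set claims to follow, and it does so in the population that carries the primary test. An FAS requiring one dose and one post-baseline evaluation would be ordinary. The problem is the higher dose threshold. This is not a detail left to a statistical analysis plan: the protocol fixes the rule, in two places.

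**Working it through.** **Inputs, all from the Protocol**
- Design (Section 11.1): difference 3 mmHg, SD 7.8 mmHg, one-sided alpha 0.025, 108 evaluable per group, stated power 0.80229; 260 enrolled, 130 per group.
- Earlier phase II trial (Section 1.2, results): 283 randomised; 282 with at least one treatment (70, 69, 73 and 70 by arm); 279 in the FAS (69, 68, 72 and 70 by arm).

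**1. The plan's own figure.** A two-sample t-test with 108 per group (noncentral t) gives power 0.803, against the stated 0.802. At 107 per group it gives 0.7997, so 108 is right. The point concerns who is analysed, and the planned size does not change.

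**2. Who is affected**

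| Subject | Safety set | FAS as written | FAS with an at-least-one rule |
|---|---|---|---|
| Randomised, no dose | out | out | out |
| One dose, no post-baseline reading | in | out | out |
| One dose, exit reading taken | in | **out** | **in** |
| Two or more doses, at least one reading | in | in | in |

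Only the third row changes with the wording.

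**3. How many that could be.** The protocol gives no count of one-dose stoppers, so the earlier trial serves as an upper guide. Taking its FAS as nested in its safety set, 282 − 279 = 3 treated subjects were outside the FAS, and 3/282 = 1.1%. The fourth randomised subject missing from the FAS (283 − 282 = 1) was never treated and would be excluded under either wording. By arm the differences are 1, 1, 1 and 0; in the 240 mg arm, 1/73 = 1.4%. That trial's FAS rule is not given, and nothing shows that these three took one dose or had a reading. The share caused by this wording could be zero.

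**4. Shift in the estimate.** Assume a fraction f of each arm is excluded, the excluded drug subjects gain nothing over placebo, the retained ones gain 3 mmHg, and the excluded placebo subjects resemble the retained ones. With everyone included the difference is 3(1 − f); with the exclusion it is 3. The overstatement is 3f:
- f = 0.011: 3 × 0.011 = 0.03 mmHg, about 1% of the planned difference.
- f = 0.014: 3 × 0.014 = 0.04 mmHg.

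The standard error of the difference with 130 per arm is 7.8 × √(2/130) = 0.97 mmHg, so 0.03 mmHg is about 3% of one standard error.

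**5. Direction.** Reverse the assumption: the excluded placebo subjects did 3 mmHg worse than the other placebo subjects, and the excluded drug subjects were typical. Exclusion then shrinks the difference by the same 3f = 0.03 mmHg. The documents do not say which pattern to expect.

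**6. Power.** 130 × 0.011 = 1.4 subjects per arm. Power is 0.871 at 130 per arm, 0.868 at 129 and 0.865 at 128, a loss of less than one percentage point.

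**The case against.** The strongest reply is that this is a translation artefact. The English is rough throughout: Chinese characters remain in the flow chart, the drug name is rendered in several ways, and Section 11.4.1 calls the primary test non-inferiority where the summary and Section 11.3 call it superiority. One or more would fit better with intention to treat and with carrying the last observation forward. That is plausible but cannot be shown from the document. The threshold appears in both definitions, while the safety set is worded with at least. If it is a slip, correcting it changes nothing that was intended.

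A second reply is that many one-dose stoppers will have no post-baseline reading and would fall outside an ordinary FAS anyway. This stands, and it is why the size above is an upper guide.

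A reader might go further in four ways that the documents do not support:
- **That more than one evaluation is also required**, so that anyone with a single reading is dropped. The summary uses the singular, and Section 11.2 attaches the threshold to the medication record alone. A subject leaving between weeks 2 and 4 with an exit reading would in any case have two evaluations.
- **That the bias favours the drug.** Early stopping on placebo, for example on reaching the blood pressure limit in the exiting criteria, would work the other way.
- **That the shift is much larger**, obtained by placing all four earlier exclusions in the drug arm and using the 240 mg arm's fall from baseline. One of the four was never treated, and an uncontrolled fall is not a difference from placebo.
- **That the FAS loses its value as a check on the per-protocol set.** That set also removes poor compliers, visits outside the window and interfering treatment, so a one-dose threshold barely narrows the contrast.

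**Conclusion.** The point holds as a minor inconsistency. As written, the main efficacy population excludes a randomised one-dose subject who has a usable blood pressure, contrary to the principle it cites and out of line with the safety set. On the earlier trial's figures the effect is about 0.03 mmHg (0.04 mmHg at the 240 mg arm's rate) and less than one point of power; it could be nil, and its direction is unknown. This rests on three assumptions: early exclusions occur at about the earlier trial's rate, all of those exclusions are attributed to this rule, and excluded drug-arm subjects have no benefit over placebo. It does not threaten the trial's conclusion. It matters because the rule decides who enters the primary test and should not depend on how one phrase is read.

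**What to change.** In the Protocol summary and in Section 11.2, replace the entry rule with: *all randomised subjects with at least one dose of double-blind drug and at least one post-baseline seated blood pressure, analysed in the group assigned*. Counting doses rather than records also removes any doubt about what counts as a record, and it aligns the FAS with the safety set and with the carrying forward of a single reading.

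The cost is one phrase in two places, with no new data, no extra subjects and no change to the sample size. A few early stoppers may re-enter, and the estimate may become slightly less favourable. The change should be made before unblinding.
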